## Abstract

**Background:**

Obese patients undergoing laparoscopic sleeve gastrectomy (LSG) are particularly at risk of opioid-related side effects. To reduce patient exposure to opioids, multimodal analgesia, which involves the use of drugs of different classes, may be utilized. One of the drugs under consideration is pregabalin. Despite an opioid-sparing potential, few studies assess the role of pregabalin as an element of multimodal analgesia in LSG. Considering the limited number and inconsistent results of available studies, we decided to conduct a randomized, prospective study on the effect of preemptive pregabalin administration in obese patients on opioid consumption, pain scores, the incidence of opioid side effects, and hemodynamical stability.

**Methods:**

The study is designed as a prospective randomized controlled trial with double-blinding. Randomization will be performed in a block with a parallel 1:1 allocation. The intervention will involve receiving a pregabalin 150 mg capsule 1–2 h before the surgery, whereas the control group will receive an identically looking placebo. The primary outcome measure will be total oxycodone consumption in the first 24 h following surgery. Secondary outcome measures will be pain severity assessed using the Numerical Rating Scale (NRS) 1, 6, 12, and 24 h after surgery, postoperative sedation on the Ramsay scale, PONV impact scale, the incidence of desaturation episodes < 94%, and episodes of blurred vision at 1, 6, 12, and 24 h after surgery, intraoperative hemodynamic parameters such as heart rate (HR), systolic blood pressure (SBP), diastolic blood pressure (DBP), mean blood pressure (MBP), total fluid volume, and total ephedrine dose. Patient comfort will be additionally assessed using the QoR-40 questionnaire at discharge.

**Discussion:**

The study will explore the efficacy and safety of preemptive pregabalin in a dose of 150 mg as a co-analgesic used in multimodal analgesia for LSG. As studies on opioid-sparing regimes concern the safety of obese patients, we aim to contribute objective data with a relatively large study sample size. The result of the present clinical trial may support the reassessment of recommendations to use pregabalin in the studied population.

**Trial registration:**

ClinicalTrials.gov NCT05804591. Registered on 07.04.2023.

**Supplementary Information:**

The online version contains supplementary material available at 10.1186/s13063-024-08225-3.

## Administrative information

Note: the numbers in curly brackets in this protocol refer to the SPIRIT checklist item numbers. The order of the items has been modified to group similar items (see http://www.equator-network.org/reporting-guidelines/spirit-2013-statement-defining-standard-protocol-items-for-clinical-trials/).

### Background and rationale {6a}

Multimodal analgesia is a technique involving different mechanisms of action, owing to which it is possible to reduce or even eliminate the intraoperative use of opioids and significantly decrease their use postoperatively. To achieve this, several co-analgesics, such as alpha-2 agonists, lidocaine, ketamine, magnesium sulfate, and gabapentinoids, are utilized. They are all part of a concept of multimodal analgesia based on addressing different pain mechanisms. The use of multimodal analgesia reduces opioid-induced side effects in the postoperative period, which is especially beneficial for obese patients with a BMI > 35 qualified for laparoscopic bariatric surgery [1, 2]. Such patients are prone to side effects of opioids, primarily respiratory complications, excessive sedation, and a high risk of postoperative nausea and vomiting, which prevent early patient recovery [3].

Pregabalin, one of the drugs used in multimodal analgesia, is a gamma-aminobutyric acid analog. It has anxiolytic, analgesic, and opioid-sparing properties and is commonly used as a first-line treatment for neuropathic pain [4]. Furthermore, it has effectively prevented opioid-induced hyperalgesia [5, 6]. These properties may prove useful in laparoscopic bariatric surgery, during which there is a risk of nerve fiber injury secondary to cutting and coagulation.

The 2018 ESRA procedure-specific postoperative pain management (PROSPECT) recommendations suggest the use of pregabalin in patients who cannot receive simple analgesics [7]. The above statement is based on two trials involving pregabalin perioperatively in patients who underwent LSG. In the study by Schulmeyer et al., a single 150 mg dose of pregabalin 2 h before surgery allowed for a decrease in the total dose of opioids administered in the postoperative period by 50%. What is essential, pregabalin did not increase the rate of experienced side effects such as excessive sedation or dizziness [8]. Nonetheless, this study has significant limitations, as the study did not implement Patient-Controlled Analgesia (PCA) and more importantly, the authors of the PROSPECT recommendations underline the lack of multimodal analgesia in both the study and control groups. In a study performed by Salama et al. [9], a 68% decrease in the total dose of opioids was possible with 75 mg of pregabalin and a dexmedetomidine infusion of 0.4 μg/kg/h. However, in this study, it is impossible to distinguish between the effects of both medications, as dexmedetomidine has also been proven to have analgesic potential. Similar difficulty in assessing the isolated pregabalin effect has been reported in the observational study by Lam et al. In their study, pregabalin, 150 or 300 mg, depending on the patient's weight, was given as an element of multimodal analgesia to reduce or eliminate total postoperative opioid use [10]. In another trial concerning pregabalin, Alimian et al. demonstrated a reduced incidence of PONV with concomitant lower pain scores throughout the postoperative period in patients undergoing laparoscopic gastric bypass surgery [11]. The limitations of this study include a lack of assessment of sedation and the effects of specific components of multimodal analgesia, which can vary depending on the procedure and may differ between types of surgeries; thus, they are not fully generalizable to patients undergoing LSG [12].

Concerning analgesic management in our study, remifentanil is a basic intraoperative opioid due to its rapid elimination and short time of action, which is in concordance with ERAS guidelines [1]. Moreover, it has been proven that these two drugs have a synergistic effect, which may be beneficial in the perioperative period but, on the other hand, may also cause an increased risk of adverse effects [13, 14]. Pregabalin also has an antihyperalgesic effect, possibly attenuating opioid-induced hyperalgesia sparked by remifentanil [6].

In addition, as pregabalin is a promising element of multimodal analgesia strategy, we plan to measure intraoperative parameters relating to patient hemodynamical stability such as heart rate (HR), systolic blood pressure (SBP), diastolic blood pressure (DBP), and mean blood pressure (MBP) every 5 min as well as cumulative doses of vasopressors needed, atropine used to treat bradycardia and administered fluid volume. In our study, we hypothesized that pregabalin might have little or no effect on hemodynamical stability in contrast with most commonly used co-analgesics such as lidocaine, dexmedetomidine, or magnesium sulfate [1, 15–18]. Its possibly negligent impact on the circulatory system would be beneficial as obese patients undergoing LSG are particularly prone to hemodynamic disturbances [19, 20], and hypotension may in these patients spark complications like myocardial infarction or kidney failure [21].

To our knowledge, there are no known studies assessing the impact of pregabalin on patient recovery after LSG, with a specific focus on its sedative effects, in isolation from other medications such as dexmedetomidine [10, 11]. As we hypothesized that pregabalin may have a beneficial impact in this field, such an effect will be measured in the postoperative period on both an objective scale and by filling out the Quality of Recovery-40 questionnaire (QoR-40), constructed to measure patient’s experience after a broad spectrum of surgeries [22].

In conclusion, considering the limited number and inconsistent results of available studies on the effect of preemptive pregabalin administration in obese patients on opioid consumption, pain scores, the incidence of opioid side effects, and hemodynamical stability, we decided to conduct our randomized, prospective, double-blind study.

### Objectives {7}

Our study aims to assess, in the patients with obesity undergoing LSG, what is the difference in total oxycodone consumption (applied by the PCA pump) between preemptive oral pregabalin 150 mg administration compared with placebo, 24 h after the operation. We hypothesized that the investigated intervention would reduce opioid use and improve recovery with potentially fewer opioid side effects, as well as provide similar intraoperative hemodynamical stability.

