### Trial design {8}

The study is designed as a double-blind, randomized superiority trial. Equal, parallel 1:1 randomization will be performed using http://www.randomization.com (Dallal GE).

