#### Statistical methods for numerical outcomes with one-time measurement

For numeric outcomes involving a single measurement point (e.g., total oxycodone consumption at 24 h, comparison of lowest and highest BP and HR values, duration of MBP below 65 mmHg or above 90 mmHg, HR below 50/min, and HR above 90/min, total fluid volume administered, total ephedrine usage during surgery, QoR-40 score at discharge), the significance of differences between the study group and the control group will be assessed using the Wilcoxon sum rank test. This non-parametric test is chosen based on the assumption that the distributions of these numerical variables do not conform to a normal distribution. For each outcome variable, the median and interquartile range (IQR) will be reported for both the study and control groups. In addition to the *p*-values, the Wilcoxon effect size (*r*) will be calculated to quantify the magnitude of the difference between the groups. Where possible, 95% confidence intervals for median differences between groups will be reported to provide an estimate of the precision of the observed effects.

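### Similar haemodynamic stability is hypothesised, but the plan offers only tests of difference and sets no margin or criterion for concluding similarity

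*Protocol article*

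**What the plan says.** The haemodynamic hypothesis appears twice. Under Objectives {7}, the intervention is expected to lower opioid use, improve recovery, "as well as provide similar intraoperative hemodynamical stability". Under Background and rationale {6a}, the authors write that "we hypothesized that pregabalin might have little or no effect on hemodynamical stability", in contrast with other co-analgesics.

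Trial design {8} states: "The study is designed as a double-blind, randomized superiority trial". Sample size {14} rests on 24-hour oxycodone alone: 76 patients, raised to 90 for drop-out.

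The section on numerical outcomes with one-time measurement covers the haemodynamic outcomes, including "comparison of lowest and highest BP and HR values, duration of MBP below 65 mmHg or above 90 mmHg". For all of them, "the significance of differences between the study group and the control group will be assessed using the Wilcoxon sum rank test". Two further outputs are planned: "the Wilcoxon effect size (*r*) will be calculated to quantify the magnitude of the difference between the groups", and "Where possible, 95% confidence intervals for median differences between groups will be reported".

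The rationale also plans to record "cumulative doses of vasopressors needed, atropine used to treat bradycardia and administered fluid volume". Outcomes {12}, the timeline table and the statistical methods carry forward only fluid volume and ephedrine. The section on statistical software says that the analysis plan is integrated in this protocol and that no separate one will be published.

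**The concern.** The hypothesis is one of no relevant difference, while the planned test looks for a difference. Failing to reject equality does not show similarity, and it happens most easily when the data are least informative. A similarity statement needs a limit fixed in advance, with the interval for the between-arm difference lying inside it. Without that limit, the planned intervals have nothing to be judged against, and none of the 14 measures is named as decisive.

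What is at stake is a safety message. The rationale links hypotension in these patients to serious complications. The Discussion says that the evidence, including that on haemodynamic stability, may contribute to a reassessment of recommendations.

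A smaller inconsistency bears on the same message. Treatment for bradycardia or hypotension can limit the recorded lowest values and shorten time below a threshold. If the arms differed in such treatment, they could look alike on those measures.

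**Working it through.** **Number of measures.** Outcomes {12} lists highest and lowest values of HR, SBP, DBP and MBP (4 × 2 = 8), four durations outside limits, total fluid volume and total ephedrine: 8 + 4 + 2 = 14.

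**The plan's own figure.** No sample size is given for the haemodynamic hypothesis. For oxycodone (difference 10 mg, SD 13.7 mg, two-sided 5%, 90% power as the Discussion states), n per arm = 2 × [13.7 × (1.960 + 1.282) / 10]² = 39.4. That rounds to 40 per arm, 80 in total, against the stated 76. At 38 per arm the same formula gives 88.9% power. The drop-out step reproduces: 76 / 0.85 = 89.4, adopted as 90. The gap between 76 and 80 does not matter here. What is needed is the range per arm: 76 / 2 = 38 evaluable and 90 / 2 = 45 randomised.

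**Assumptions.** The documents give no haemodynamic SD or margin, so differences and margins are in SD units over an assumed range. With n per arm, SE = √(2/n): 0.229 at 38 and 0.211 at 45.

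**Precision.** Half-width of the 95% interval = t(0.975, 2n − 2) × SE, which is 0.46 SD at 38 per arm and 0.42 SD at 45.

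**Chance of a non-significant result when a difference exists** (two-sided 5%, t-test approximation):

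| True difference | 38 per arm | 45 per arm |
|---|---|---|
| 0.3 SD | 75% | 71% |
| 0.4 SD | 59% | 53% |
| 0.5 SD | 42% | 35% |

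Multiplying n by 3/π for the Wilcoxon test's efficiency under normality gives 76% / 72% at 0.3 SD and 44% / 37% at 0.5 SD. The picture does not change.

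**Power to show equivalence when the true difference is zero** (normal approximation): 2Φ(margin/SE − z) − 1, with z = 1.645 for a 90% interval (two one-sided 5% tests) and z = 1.960 for a 95% interval. For example, at 38 per arm with a 0.5 SD margin and a 90% interval: 0.5 / 0.229 = 2.18; 2.18 − 1.645 = 0.53; 2Φ(0.53) − 1 = 0.41.

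| Margin | Interval | 38 per arm | 45 per arm |
|---|---|---|---|
| 0.5 SD | 90% | 41% | 53% |
| 0.5 SD | 95% (as planned) | 17% | 32% |
| 0.7 SD | 90% | 84% | 91% |
| 0.7 SD | 95% (as planned) | 72% | 83% |

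With a 0.5 SD margin and a 90% interval, 80% power would need 69 per arm. Both the margin and the interval level therefore decide whether the claim is reachable.

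**The case against.** A reader might infer that the sponsor will declare similarity whenever p exceeds 0.05. The documents do not say so. The rationale is hedged, and the Discussion promises only evidence on haemodynamic stability. What stands is narrower: a similarity hypothesis is stated and no criterion for it is given.

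Nor is the p-value the only planned output. Effect sizes and, where possible, 95% intervals are also promised. A careful report could rest on those intervals, so part of the remedy is already in the plan. The limit to judge them against is still missing, and *where possible* leaves room for them to be omitted.

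The figures are in assumed SD units and use a normal or t approximation, while the plan itself expects non-normal data. They transfer poorly to a skewed duration such as time with low MBP. The 38-per-arm column may also be pessimistic, because these outcomes are recorded during surgery and little missing data is expected. The 45-per-arm column answers that, and the conclusion is the same.

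A reader might also infer that leaving out atropine and vasopressors conceals an effect. The documents do not support this: use of such drugs, and any imbalance, is unknown. Ephedrine is the only vasopressor named, and its total dose is analysed. The atropine discrepancy is real; the vasopressor part is weaker.

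Finally, this is a secondary hypothesis in a trial declared as superiority on oxycodone, which limits how much the defect matters.

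**Conclusion.** The point holds in this form: the planned analysis cannot answer the stated similarity hypothesis, because it tests for a difference and sets no margin or decision rule. Leaving this to a separate analysis plan is not a defence, since the protocol says its plan is integrated.

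If non-significance were used as the criterion, it would be weak evidence: with 38 to 45 per arm, 35–42% of trials would miss a true 0.5 SD difference and 71–75% a 0.3 SD difference. A formal similarity claim is within reach only for a wide margin. At 0.7 SD, power is 84–91% with a 90% interval and 72–83% with the planned 95% interval. These sizes rest on assumed SD units, approximate normality and, for equivalence, a true difference of zero; any real difference would lower the equivalence power. The primary conclusion on oxycodone is not touched.

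**What to change.** Before unblinding, take one of two routes.

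(a) Name one key haemodynamic measure already collected. Have the investigators fix a similarity margin in that measure's own units, and state the interval level. Conclude *similar* only if the interval for the between-arm difference lies inside the margin. Report the other measures with intervals only.

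(b) Restate the haemodynamic aim as estimation. Report the interval for every haemodynamic measure rather than only where possible. State that a non-significant result will be reported as no difference detected, not as similarity.

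Under either route, reconcile the rationale with Outcomes {12} and the statistical methods by adding atropine use, and any vasopressor other than ephedrine, to the analysed outcomes.

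The cost is wording and, under (a), one agreed margin, plus the amendment steps that the protocol already describes. No new patients are needed, and no new data beyond what the rationale already plans to record. The downside is that a similarity claim may prove out of reach.

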### Trial design {8}

The study is designed as a double-blind, randomized superiority trial. Equal, parallel 1:1 randomization will be performed using http://www.randomization.com (Dallal GE).

## Methods: participants, interventions, and outcomes

### Study setting {9}

Academic Hospital in Warsaw, Poland.

### Eligibility criteria {10}

Eligible patients should have a BMI > 40 or > 35 with comorbidities, be 18 to 65 years old, and be LSG-eligible. Patients aged above 65 years are rarely qualified for LSG, and the elderly have a higher risk of unwanted effects [23]. Patients who did not agree to participate in the study, are undergoing revision surgery, have an allergy to any of the drugs used in the protocol, have end-stage organ failure, are unable to cooperate in assessing pain intensity on the numerical rating scale (NRS) scale or use a PCA pump will be excluded from the study.

### Who will take informed consent? {26a}

The consent will be taken by one of the four dedicated investigators, trained before by the principal investigator**.** The approach for consent will be made in the hospital 1 day before the scheduled surgery. One of the investigators will provide the potential participant with a description of the study, potential risks, their rights as a participant, other relevant details and take informed, written consent on a prepared consent form. They will also hand the participant information leaflet. At the time of obtaining the consent for study inclusion, the patient will have a chance to ask questions.

### Additional consent provisions for collection and use of participant data and biological specimens {26b}

No blood samples will be obtained in our study. All participants should give informed, written consent to the research team to share relevant data with researchers taking part in the research, as well as regulatory authorities. This information will be explained to participants and made available on the consent form. All participants should agree to the above.

## Interventions

### Explanation for the choice of comparators {6b}

Participants will be randomized into two groups: pregabalin and control. They will receive identically looking capsules 1–2 h before the operation. According to Enhanced Recovery After Bariatric Surgery (ERABS) protocols or European Society of Regional Anaesthesia and Pain Therapy (ESRA) guidelines, no pharmacological agent should be compared to the test drug [7]. Therefore, we will choose a placebo as a comparator. As the sedative effect of pregabalin is dose-related, and a dose of 300 mg may produce a clinically relevant level of sedation, we will investigate a lower dose of 150 mg [1, 7, 24].

The intervention and placebo are produced in our hospital pharmacy department by dedicated hospital pharmacists and trained pharmaceutical technicians. The original capsule containing pregabalin is dismantled and the drug is placed in the capsule used for our trial, identically looking for the intervention and placebo group. Lactose is used as a standard excipient in both groups. Therefore, it is not possible to discern the capsules on appearance or taste. The capsules are prepared in a dedicated room, with temperature, humidity, and light conditions complying with the requirements for drug manufacturing and storage**.** To ensure the quality of the capsules during their manufacturing, the weight of the capsule fill is monitored, and a visual inspection is performed.

### Intervention description {11a}

The Pregabalin group will receive a capsule containing 150 mg pregabalin as a single dose 1–2 h before the surgery, whereas the control group will receive a same-looking capsule with a placebo. Lactose will be used as a standard excipient in all capsules. The capsule composition does not include dyes, preservatives, or additives, guaranteeing a standard, identical appearance. The capsule has a volume of 0.36 ml, ensuring ease of swallowing. The expiratory date is 1 month after production by our hospital pharmacy.

### Criteria for discontinuing or modifying allocated interventions {11b}

Patients will be free to withdraw from the study at request at any time. Theoretically, in rare cases, it is possible that after randomization and receiving the placebo or intervention, the patient would be disqualified from the surgery or anesthesia due to some impossible-to-predict medical factors that would be revealed immediately before the scheduled operation or will not be able to complete the study treatment. In such a case, they would be withdrawn from the “as treated” analysis of the study outcomes.

### Strategies to improve adherence to interventions {11c}

The intervention will be administered to the participant only once during the hospital stay, and this fact is noted in their individual medication chart. Therefore, participants’ adherence to interventions will be assured.

### Relevant concomitant care permitted or prohibited during the trial {11d}

Patients will continue their concomitant treatment due to chronic diseases in the perioperative period unless it is contraindicated in the planned surgery or anesthesia.

